### Power analysis

The power calculation for our *primary outcome* takes into consideration analyses involving comparisons of means and proportions. In making these power calculations, we assume that two therapists in each group (four in total) will either “drop out” of the project, change jobs, or leave VA employment, leaving us with a sample size of 30. With a sample size of *n* = 30 therapists, we will have an 84 % power to detect a large effect size (Cohen’s *d* = 1.0) in mean treatment fidelity based on all sessions from each therapist’s mid and last patients. This calculation assumed a 1.2 point difference in mean fidelity between the intervention and control groups, a pooled standard deviation of 1.2, alpha = 0.5, and a two-tailed test of significance. With a sample size of *n* = 30 providers, we will also have 88 % power to detect a 35 % difference (85 versus 50 %) in the proportion of therapists maintaining minimally acceptable treatment fidelity between the intervention and control groups based on all sessions from each providers mid and last patients. This calculation assumed a 0 % attrition rate, alpha = 0.05, and a two-tailed test of significance.

It will not be necessary for patients to complete a full course (eight sessions) of CBT to be included in the study so we expect minimal “drop out” of patients. The power calculation for our *secondary outcome* must take into account the clustering of patients with providers. Prior psychotherapy RCTs have found intraclass correlation coefficients to vary widely (range 0 to 0.73) with a mean of about 0.08 [41]. We based our power analysis on a slightly conservative intraclass correlation coefficient of 0.10. With a sample size of *n* = 300, we will have 85 % power to detect a medium effect size (Cohen’s *d* = 0.5) for our secondary outcome of overall mental health functioning [42].

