### Data analysis

Providers will be the unit of the intent-to-treat analysis for measuring our primary (fidelity to the CBT model) and secondary (mental health) outcomes. For our primary outcomes, the dependent variable will be the composite fidelity score from each provider’s midpoint and last patient. The composite score will be calculated as the mean of the two scores. A dummy variable representing treatment group assignment will be specified as the explanatory variable of interest. An alpha significance level of 0.05 will be used to reject/accept the null hypothesis. Study hypotheses will be tested using a standard logistic regression model. Three covariates will be specified to control for differences across providers. We will first examine differences in the characteristics of providers across the intervention and control group and include those characteristics that differed statistically. If no group differences are observed in the characteristics of the providers, we will control for previous CBT experience (none, some, most experience) and length of time in clinical practice. To examine our secondary outcomes, overall mental health functioning will be measured at baseline and at 3 and 6 months follow-up. Patients will also be screened for any of five specific disorders at baseline (PTSD, PD, GAD, SAD, and comorbid depression); and for those who score positive in a given disorder, ongoing assessment of that disorder will continue through the study. We expect a high degree of comorbidity, so participants will choose the disorder that is bothering them the most as the “target” disorder for CBT treatment.

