### Aim 3: implementation needs assessment

Our research partners in VA Central Office are interested in adopting the CALM tool for use in the VA, especially in CBOCs. If the CALM tool improves fidelity to the CBT model, our VA partners will help us pave the way for national rollout. To help prepare for the future implementation of the tool in routine care, we will perform an implementation needs assessment with key stakeholders—CBOC mental health providers participating in aim 2 and their CBOC directors.

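### The article does not consistently fix which contrast, mean composite fidelity or proportion with acceptable fidelity, decides the primary hypothesis

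*Protocol article*

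**What the plan says.** All of this is in the Protocol article, under Aim 2 unless noted.

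- **Outcome.** Fidelity assessments says that the domain ratings, each on a 1 to 7 scale, are combined into one fidelity measure. Fidelity ratings makes the midpoint and last patient of each therapist the primary outcome measure.
- **Dependent variable.** Data analysis: "For our primary outcomes, the dependent variable will be the composite fidelity score from each provider’s midpoint and last patient". It adds: "The composite score will be calculated as the mean of the two scores". This is a continuous score, one per provider.
- **Test.** The same section: "Study hypotheses will be tested using a standard logistic regression model".
- **Alpha.** Stated once there: "An alpha significance level of 0.05 will be used to reject/accept the null hypothesis".
- **Power.** Power analysis says that the primary-outcome calculation "takes into consideration analyses involving comparisons of means and proportions". With 30 therapists it gives 84 % power for a mean difference of 1.2 (SD 1.2, d = 1.0). It also gives 88 % power for a difference of 85 versus 50 % "in the proportion of therapists maintaining minimally acceptable treatment fidelity between the intervention and control groups". The means calculation prints alpha as 0.5; the proportions calculation prints 0.05. Both are two-tailed.
- **Use of the result.** The Aim 3 section says: "If the CALM tool improves fidelity to the CBT model, our VA partners will help us pave the way for national rollout".

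The proportion is not defined as an outcome anywhere outside Power analysis, and the article gives no cut-off for acceptable fidelity on the 1 to 7 scale.

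**The concern.** The fidelity hypothesis in the Aim 2 introduction is that tool providers will show higher fidelity than manual providers. It does not say on which scale. The named dependent variable points to a comparison of means, the named model points to a comparison of proportions, and the power section puts the two side by side under the primary outcome.

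Two things are at stake. One is that with about 15 providers per arm the two contrasts can give different answers from the same data, so the trial's main result may depend on which is reported as primary. The other is that if both were run at 0.05 and the favourable one were reported, the error rate would exceed the stated alpha. The national rollout depends on the answer.

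**Working it through.** **Inputs.** From Power analysis: 34 providers less two per group leaves 30, taken as 15 per arm (equal allocation inferred). Mean difference 1.2, SD 1.2; proportions 0.85 and 0.50; two-tailed. Alpha is 0.05 from Data analysis, because the 0.5 printed for means conflicts with it and is probably a misprint. Assumed: normal scores, no covariates, the same score used for both tests, and a cut-off as stated below.

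**The plan's own power figures.**

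Means, normal approximation: power = Φ(d·√(n/2) − 1.96) = Φ(1.0 × √7.5 − 1.96) = Φ(0.779) = 78.2 %. With the t distribution it is 75.3 %. The stated figure is 84 %. At the printed alpha of 0.5, power would be 98 %.

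Proportions, pooled test, p̄ = (0.85 + 0.50)/2 = 0.675:
- null SE = √(2 × 0.675 × 0.325 / 15) = 0.171
- alternative SE = √((0.85 × 0.15 + 0.50 × 0.50)/15) = 0.159
- power = Φ((0.35 − 1.96 × 0.171)/0.159) = Φ(0.093) = 53.7 %

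Other variants give 37.1 % (Fisher) to 59.7 % (unpooled). The stated figure is 88 %. So neither figure reproduces at 15 per arm. That is a separate matter, but it bears on the choice of contrast: on the stated inputs the mean comparison is the better powered.

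**What the text fixes, side by side.**

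| Element | Points to means | Points to proportions |
|---|---|---|
| Dependent variable (Data analysis) | yes | no |
| Model (Data analysis) | no | yes |
| Power analysis | yes | yes |
| Rank or rule between them | none | none |

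**Error rate if both tests were run and either counted.** P(either) = P(A) + P(B) − P(both). Independent tests would give the ceiling, 1 − 0.95² = 9.75 %. The two tests share the same scores, so the rate was simulated with no true effect and 15 per arm.

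| Binary test paired with the t-test | Assumed share acceptable | P(either), two-sided |
|---|---|---|
| Pooled chi-square | 50 to 85 % | 7.3 to 8.3 % |
| Wald logistic | 50 to 69 % | 6.3 to 7.1 % |
| Fisher exact | 50 to 85 % | 5.5 to 5.7 % |

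Example, chi-square at 50 %: 4.98 % + 4.48 % − P(both) = 7.33 %, so both are significant in 2.13 % of trials. The tests overlap heavily, which is why the inflation is modest.

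**Disagreement at the planned effect.** With d = 1.0 and the cut-off assumed at the control mean, the shares are 50 % in control and Φ(1.0) = 84 % in the tool arm, close to the planned 85 versus 50 %.

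- t-test power 75.3 %, chi-square 54.0 %, disagreement 27 %. Mean-only minus proportion-only is 75.3 − 54.0 = 21.3 points and their sum is 27, so mean-only is about 24 % and proportion-only about 3 %.
- With Wald logistic, power is 38.0 % and disagreement 40 %. By the same arithmetic, mean-only is about 39 % and proportion-only about 1 %.

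Most of the disagreement is therefore a true effect that the mean comparison finds and the dichotomised test misses.

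**The case against.** A reader might infer that the plan sets up two deciding tests, each at full alpha 0.05, and lets the claim rest on either one. The documents do not support that. Fidelity assessments, Fidelity ratings and Data analysis together designate one fidelity measure, one dependent variable and one alpha; the plural in "For our primary outcomes, the dependent variable will be the composite fidelity score from each provider’s midpoint and last patient" is followed by a single variable. The proportion appears only in a sample-size justification, and powering an outcome on two scales does not make both tests decisive. The alpha printed for means is not even 0.05. Nowhere does the article say that success on either test suffices.

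The size should not be overstated either. Logistic regression is the only method the article names, and with a Wald test from it the rate is about 6.3 to 7.1 %. These rates count both directions. By symmetry a false finding in favour of the tool is half of them, about 2.8 to 4.2 % (5.5/2 to 8.3/2), against a nominal 2.5 %. Larger figures need a search over several cut-offs, which nothing in the article suggests.

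It can also be said that labelling a supportive analysis and fixing its cut-off belong in the statistical analysis plan. That is fair for the cut-off taken alone, and its absence is not the defect here.

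What the objection does not remove is the contradiction in the text. The section that would settle the matter pairs a continuous score with a binary-outcome model, and the next section powers both contrasts as the primary outcome. Correcting the model alone would still leave the second powered comparison without a status.

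**Conclusion.** The point holds as an inconsistency about which contrast is primary, not as a declared multiplicity. The possible inflation is modest: about 5.5 to 8.3 % two-sided, conditional on both tests being run at 0.05 and either being accepted, which the article does not state. The stronger practical reason to act is that at d = 1.0 the two contrasts would disagree in about 27 % (chi-square) to 40 % (Wald logistic) of trials. These figures rest on 15 providers per arm, normal scores, no covariate adjustment and, for the disagreement, an assumed cut-off at the control mean. The point should be corrected before analysis; it does not call the design into question.

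**What to change.** In Data analysis and Power analysis, state that the single primary analysis is the between-arm difference in mean composite fidelity (mean of midpoint and last patient), tested at two-sided alpha 0.05 with a model suited to a continuous score, such as a linear model with the planned covariates, in place of the logistic model. Use the singular for the primary outcome. Label the comparison of proportions supportive, at one cut-off specified in advance, and treat it as confirmatory only if the mean comparison is significant.

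This uses the outcome that the article already defines and keeps the better-powered contrast (about 75 % against 38 to 54 % for the dichotomised score in the scenario above). It holds alpha at 0.05 without a split. Splitting alpha to 0.025 each would instead leave about 65 % power for means (t-test) and 42 % for proportions (pooled test, 85 versus 50 %).

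The cost is a few sentences, with no added providers or data. The small downside is that the proportion result alone could no longer support the primary claim.

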### Study participants

Participants will include mental health providers and veteran patients. We will recruit 34 mental health providers (all disciplines eligible) to receive training in CBT. Upon completion of training, each mental health provider will invite ten of his/her patients to participate in CBT treatment (Table 1).

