#### Fidelity ratings

Fidelity assessments will focus on therapy sessions delivered early and late in the project. Fidelity for the first patient will be assessed and used to control for initial group differences in multivariate analyses. We expect each therapist to see ten patients each, with each patient completing up to eight sessions. Fidelity will be assessed only for patients who have attended at least four sessions. Fidelity will be measured for a “midpoint” patient (patient four or five of ten) and the last patient receiving at least four treatment sessions from each therapist. Fidelity for the midpoint and last patient for each therapist is our primary outcome measure. A single overall fidelity rating will be completed for each (midpoint and last) patient’s last three sessions. A minimum of 5 % of the total sessions being analyzed will be randomly selected to be rated by both raters to characterize inter-rater reliability.

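### The 84 % power stated for the primary comparison of mean fidelity does not follow from its own inputs: with 15 therapists per arm and a two-tailed 0.05 test it is about 75 %

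*Protocol article*

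**What the plan says.** The section on Aim 2 study participants sets recruitment: "We will recruit 34 mental health providers (all disciplines eligible) to receive training in CBT". The Power analysis section allows for losses ("we assume that two therapists in each group (four in total"), "leaving us with a sample size of 30". For that number it says "we will have an 84 % power to detect a large effect size", given as Cohen's d of 1.0. The stated inputs are a 1.2-point difference in mean fidelity and "a pooled standard deviation of 1.2, alpha = 0.5, and a two-tailed test of significance".

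The Data analysis section of Aim 2 sets the significance level at 0.05. The calculation for proportions, which comes next in the Power analysis section, also uses 0.05, two-tailed.

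On the quantity being compared, the power calculation speaks of a difference "in mean treatment fidelity based on all sessions from each" therapist's mid and last patients. The Fidelity ratings section defines the measure differently: "A single overall fidelity rating will be completed for each (midpoint and last) patient’s last three sessions". The Data analysis section then averages the two patients' scores into one value per provider.

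**The concern.** Every input to a two-sample power calculation is given, so the 84 % can be checked directly. Two features prompt the check. The printed alpha is ten times the level set elsewhere, and 84 % looks high for 15 per arm at d = 1.0 with a two-tailed test. There is also a mismatch of definition: the power section and the fidelity section do not describe the same outcome measure.

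This is one of two calculations offered for the primary outcome, and it is the one that matches the continuous composite score named as the dependent variable. If the figure is too high, readers of a null result will underestimate how likely the trial was to miss the effect it was planned around. That matters here because the article links a national rollout to whether the tool improves fidelity.

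**Working it through.** **Inputs**

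- Providers recruited: 34 (Aim 2, Study participants). Two are lost per group, leaving 30 (Power analysis). Equal allocation is inferred from the equal losses, so n = (34 − 4)/2 = 15 per arm.
- Difference 1.2 and SD 1.2 (Power analysis), so d = 1.2/1.2 = 1.0.
- Two-tailed test (Power analysis).
- Alpha: 0.5 as printed in this calculation; 0.05 in the Data analysis section and in the calculation for proportions.

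**Formulas**

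Noncentrality: λ = d × √(n/2) = 1.0 × √7.5 = 2.739, with 2n − 2 = 28 degrees of freedom.

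Exact two-sided power = P(T > t_crit) + P(T < −t_crit), where T is noncentral t with 28 df and noncentrality λ. Normal approximation: power ≈ Φ(λ − z_crit).

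**Attempt to reproduce 84 % from the stated inputs**

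| Reading | Critical value (t; z) | Noncentral t | Normal approximation |
|---|---|---|---|
| Alpha 0.05, two-tailed, 15 per arm | 2.048; 1.960 | 75.3 % | Φ(2.739 − 1.960) = Φ(0.779) = 78.2 % |
| Alpha 0.5 as printed, two-tailed, 15 per arm | 0.683; 0.674 | 98.0 % | 98.0 % |

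Neither gives 84 %. Equal arms are the most favourable split of 30: 14 against 16 gives 75.1 %, and 10 against 20 gives 70.3 %. Spending one to four degrees of freedom on covariates, with no gain in precision, leaves power at about 75 %.

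**Departures from the stated inputs that come near 84 %**

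| Departure | Power | What it contradicts or adds |
|---|---|---|
| One-sided 0.05, 15 per arm, t | 84.8 % | The text says two-tailed |
| Two-tailed 0.05, 17 per arm, normal approximation: Φ(√8.5 − 1.960) = Φ(0.955) | 83.0 % (80.7 % by t) | The text says 30 after losses |
| Two-tailed 0.05, 15 per arm, covariate correlated 0.45 with the outcome, t | 84.1 % | No such assumption is stated |

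**Effect detectable with the stated design**

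Solving the noncentral t equation for 80 % power with 15 per arm, two-tailed 0.05, gives d = 1.06, which is 1.06 × 1.2 = 1.27 points.

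**Outcome basis**

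The power section uses all sessions of the mid and last patients. The Fidelity ratings section expects up to eight sessions per patient, admits patients with at least four, and rates only the last three, with one overall score. These are different measures. The article does not say which of them the SD of 1.2 describes, or where that SD comes from, so no power figure can be attached to the difference.

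**The case against.** The strongest reply is that the planned analysis is not an unadjusted t-test. The Data analysis section specifies three covariates, and the Fidelity ratings section says first-patient fidelity will be used to control for initial differences. Adjustment could raise power above 75 %. That is fair, and it limits the claim: 75 % is the power of the calculation that the article describes, not necessarily of the final model. It does not validate 84 %, because the power section states no assumption about variance explained.

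A second reply is that alpha = 0.5 is plainly a typing error. That also stands. It adds nothing to the seriousness of the point, and correcting it leaves 84 % unsupported.

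Two stronger readings are tempting, and the article supports neither:

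- A reader might infer that a one-sided test was run, since that gives 84.8 %. But the text says two-tailed, 84.8 % rounds to 85 rather than 84, and other routes come about as close. The origin of the figure is unknown.
- A reader might infer that an SD for all sessions is too small for a rating of three sessions, so that true power is below 75 %. The source of the SD is not given, and the measure is a single overall rating, not an average of session scores. A model of averaging over sessions would rest on assumed session counts and correlations. The wording conflict is real; its size is not determinable.

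Finally, this is not the only stated basis for 34 providers, since a calculation for proportions accompanies it. That bears on emphasis, not on whether this figure is right.

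**Conclusion.** The point holds as a reporting error in the primary power statement. On the article's own inputs and its alpha of 0.05, power is about 75 % (78 % by the normal approximation), a shortfall of 6 to 9 percentage points. The corresponding type II error is about 25 % (22 % by the approximation) instead of 16 %. With 15 per arm the noncentral t figure is the appropriate one. The result assumes equal allocation, an unadjusted comparison of provider means and the stated d of 1.0.

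Separately, the power section and the Fidelity ratings section define the outcome differently and must be reconciled. No direction or size for the effect of this on power is claimed.

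**What to change.** In the Power analysis section:

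1. Print alpha as 0.05.
2. Replace 84 % with about 75 % for d = 1.0, 15 therapists per arm, two-tailed. Equivalently, state that the effect detectable with 80 % power is d = 1.06, about 1.27 points.
3. Replace the reference to all sessions with the measure defined in Fidelity ratings, or amend that section if all sessions are intended, and state which measure the SD of 1.2 describes.

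The effect size should not be raised, nor a covariate gain introduced after the fact, merely to keep 84 %; the article justifies neither.

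The cost is a corrected paragraph and a less favourable stated power. No additional providers are needed, and the correction does not itself change the planned analysis.

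### The stated 88 % power for 85 versus 50 % of therapists does not follow from 30 providers in total; with 15 per arm it is about 54 to 60 % (37 % with Fisher's exact test)

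*Protocol article*

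**What the plan says.** The Aim 2 section on study participants sets recruitment: "We will recruit 34 mental health providers (all disciplines eligible) to receive training in CBT". The Power analysis then assumes that two therapists per group are lost, "leaving us with a sample size of 30". For the mean fidelity score it claims 84 % power at Cohen's d = 1.0. For the share of providers who reach the minimum fidelity standard, its claim, made for the same 30 providers, is: "we will also have 88 % power to detect a 35 % difference (85 versus 50 %) in the proportion of therapists". The conditions of that calculation are given separately: "This calculation assumed a 0 % attrition rate, alpha = 0.05, and a two-tailed test of significance".

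The Aim 2 Data analysis section makes the provider the unit of analysis. It averages the midpoint and last patient into one composite score per provider and names logistic regression as the test of the study hypotheses.

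**The concern.** A difference of 35 percentage points is large, but 15 providers per arm is a very small sample for a binary comparison, and 88 % is not plausible on its face.

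The figure matters for how a null result would be read. The Power analysis places this comparison under the primary outcome, and logistic regression, the only test named, needs a binary outcome. A reader told that power is 88 % expects a true difference of this size to be missed 12 % of the time. If the real figure is 54 to 60 %, it is missed 40 to 46 % of the time, and 63 % of the time with Fisher's exact test. The introduction to Aim 3 links the national rollout to whether the tool improves fidelity, so an inconclusive result could be mistaken for evidence against it.

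**Working it through.** **Inputs**
- Proportions: p1 = 0.85, p2 = 0.50, difference 0.35 (Power analysis).
- Alpha 0.05, two-tailed, no further attrition (Power analysis).
- Total providers: 34 − 4 = 30 (Aim 2 Study participants; Power analysis).
- Per arm: n = 15. The allocation ratio is not stated, so equal arms are an assumption. It is suggested by the equal loss in the two groups: "two therapists in each group (four in total) will either “drop out” of the project, change jobs, or leave VA employment, leaving us with a" total of 30.
- Unit: the provider, one outcome each (Aim 2 Data analysis).

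**Formulas**

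Pooled z: power = Φ{[0.35 − 1.96·√(2p̄(1−p̄)/n)] / √([p1(1−p1)+p2(1−p2)]/n)}, with p̄ = 0.675.

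Unpooled z: power = Φ{0.35/√([p1(1−p1)+p2(1−p2)]/n) − 1.96}.

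The variance terms are 2 × 0.675 × 0.325 = 0.43875 and 0.1275 + 0.25 = 0.3775.

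**Attempt to reproduce the stated 88 % at 15 per arm**
- Null SE = √(0.43875/15) = 0.1710; alternative SE = √(0.3775/15) = 0.1586.
- Pooled: (0.35 − 1.96 × 0.1710)/0.1586 = 0.093, and Φ(0.093) = 53.7 %.
- Unpooled: 0.35/0.1586 − 1.96 = 0.246, and Φ(0.246) = 59.7 %.
- Other two-sided methods: arcsine 56.5 %, exact power of the uncorrected chi-square 56.8 %, likelihood ratio 56.9 %, continuity-corrected 37.2 %, Fisher's exact 37.1 %.

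The stated figure is not reproduced.

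**Other readings of the inputs**
- All 34 retained (17 per arm): 59.3 % pooled, 65.1 % unpooled.
- Unequal splits of 30, from 8/22 to 22/8: at most 54.5 % pooled and 60.9 % unpooled.
- One-sided 0.05 at 15 per arm: 66.7 % pooled, 71.3 % unpooled.

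None comes near 88 %.

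**What does give 88 %**

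| Providers per arm | Pooled z | Unpooled z | Fisher |
|---|---|---|---|
| 15 | 53.7 % | 59.7 % | 37.1 % |
| 17 | 59.3 % | 65.1 % | 45.7 % |
| 30 | 84.3 % | 87.7 % | 77.7 % |
| 34 | 88.7 % | 91.3 % | 83.7 % |

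Solving the unpooled formula for 88 % gives n = 0.3775 × (1.960 + 1.175)² / 0.35² = 30.3 per arm. The pooled formula needs 34 per arm. Within one formula, the pairs are 54 % now and 34 per arm needed (pooled), or 60 % now and 30 to 31 per arm needed (unpooled).

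**The neighbouring figure for means**

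For d = 1.0 and 15 per arm, a two-sided 0.05 t-test (28 degrees of freedom, noncentrality √(15/2) = 2.74) has 75.3 % power. The normal approximation gives 78.2 %. Neither is the stated 84 %; a one-sided 0.05 t-test gives 84.8 %. The alpha printed in that sentence is 0.5, which would give 98 %.

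**The case against.** The best defence is that the power sentence bases the proportion on all sessions from two patients per provider. Fifteen providers with two patients each make 30 observations per arm, and the unpooled formula then gives 87.7 %. This may be how the 88 % arose, but it does not rescue it. The endpoint is a proportion of therapists, and the Data analysis section reduces the two patients to one score per provider. More sessions make each provider's classification more reliable; they do not add providers.

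Three further points stand in part.

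- The proportion is not clearly the primary analysis. The dependent variable is a mean composite score, and the Power analysis says only that it considers both means and proportions. Against that, the named test is logistic regression, so the role of the proportion is left unsettled.
- Covariate-adjusted logistic regression was not modelled here. The article does not say that its own figure rests on that model.
- A reader might infer that the paragraph contradicts itself, because it gives a dichotomised outcome more power (88 %) than the mean (84 %). A shift of d = 1.0 cut at the control mean would give 84 versus 50 %, close to the assumed contrast. That argument needs normal scores with equal spread and a threshold at the control mean. The article states no threshold and does not derive 85 versus 50 % from d = 1.0. Its benchmark of 84 % is also doubtful. The article does not support calling this a contradiction, and the finding does not need it.

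**Conclusion.** The stated 88 % is wrong for the design described. With 30 providers in total, power is about 54 to 60 % by the uncorrected two-sided methods and 37 % with Fisher's exact test. The overstatement is 28 to 34 percentage points for the uncorrected methods and 51 for Fisher. The result assumes equal arms, the provider as unit, and the article's own proportions and alpha; no unequal split of 30 that was checked changes it.

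It is tempting to say that the total was entered as the per-arm size. The 87.7 % at 30 per arm fits that, but it fits counting two patients per provider as independent units equally well, and the document does not show which happened. Nor does the finding establish that the trial must recruit more providers. It shows that one power statement is unsupported.

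**What to change.** In the Power analysis, replace the 88 % with about 54 to 60 % (37 % with Fisher's exact test) for 15 providers per arm, state the per-arm size, and name the formula used. Do not describe the proportion comparison as adequately powered.

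Do not shift the design justification to the mean comparison while its 84 % stands. That figure should be corrected in the same edit, to about 75 % for a two-sided 0.05 t-test with d = 1.0 and 15 per arm.

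The cost is a few reworded sentences and less favourable stated figures. The correction itself needs no extra providers.
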